## Monitoring

### Data monitoring and auditing

A data monitoring committee (DMC) consisting of surgeons, statisticians and ethics experts was established to improve the quality of this trial. The DMC remains independent of the research team of the project in order to objectively evaluate the effectiveness and safety. The interim analyses will be performed when half of the estimated participants (n = 159) are enrolled, and then important decisions will be made regarding whether to “continue the trial”, “continue the trial after adjusting the protocol” or “terminate the trial”. The results of the interim analysis will be released to all investigators. The auditing will be executed monthly by DMC based on CRFs and the EDC system.

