### Sample size

The sample size calculation was based on postoperative infection. Based on the results of our previous single-center RCT, the rates of postoperative infectious complications were 39.4% in the control group and 15.2% in the probiotic group. Given a significance one-sided level of *α* = 0.025 and test efficiency of 1 − *β* = 80%, a loss adjustment of 10% and a superiority threshold of 10%, the total sample requires at least 318 patients (159 in the test group and 159 in the control group on a 1:1 allocation ratio). The Test for Two Proportions (Non-Zero Null Hypothesis[Differences]) was used for sample size calculation (Hintze, J. (2011). PASS 11. NCSS, LLC. Kaysville, Utah, USA. www.ncss.com/).

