### Statistical methods

The Shapiro‒Wilk test will be used to verify the normality of the quantitative variables. To describe the quantitative variables, the mean and SD will be used, and the median and interquartile range will be used for those variables that do not follow a normal distribution. For qualitative variable descriptions, frequencies and percentages will be used. A contrast test of proportions will be based on the *χ*^*2*^ test or Fisher’s exact test. Quantitative variables will be analyzed by Student’s *t* test or two-way repeated-measures analysis. The Mann‒Whitney *U* test will be used for variables that do not follow a normal distribution. The results will be analyzed using SPSS version 24 (IBM, Armonk, NY, USA), and *P* < 0.05 will be considered statistically significant. The mean of each variable will be used to replace missing data.

A modified intention-to-treat analysis (mITT) and per-protocol (PP) analysis will be used to compare outcomes, but the conclusion will be drawn from mITT analysis.

The mITT population is defined as subjects who are screened by investigators according to the inclusion and exclusion criteria, randomized into certain groups and receive at least one intervention. The PP population is defined as those who complete the given intervention, adhere to the study protocol and complete the data collection. Subgroup analysis will be executed based on the operation platform (laparoscope or DaVinci surgical robot), preoperative chemotherapy regimens (SOX, DOS, XELOX, FLOT or others), GI restruction and resection range (proximal, distal or total gastrectomy).

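### An interim look at effectiveness that can end the trial sits beside a one-look alpha of 0.05, and its enrolment trigger yields well under half the outcome data

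*Protocol article*

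**What the plan says.** All places are in the protocol article.

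- **Data monitoring and auditing.** The data monitoring committee is independent "in order to objectively evaluate the effectiveness and safety". On timing: "The interim analyses will be performed when half of the estimated participants (n = 159) are enrolled". The possible decisions are "continue the trial”, “continue the trial after adjusting the protocol” or “terminate the trial". No criterion is attached to any of the three. Interim results go to all investigators.
- **Sample size.** "Given a significance one-sided level of *α* = 0.025 and test efficiency of 1 − *β* = 80"%, with a 10-point superiority margin and 10% loss, gives 318 patients. On the assumed rates: "the rates of postoperative infectious complications were 39.4% in the control group and 15.2% in the probiotic group".
- **Statistical methods.** One threshold is given for all analyses: P below "0.05 will be considered statistically significant". Its sidedness is not stated.
- **Outcomes, Eligibility criteria, Trial design, Recruitment.** The primary outcome runs to 30 days after surgery. Chemotherapy ends 3-6 weeks before surgery, and the intervention starts when chemotherapy ends. Recruitment was expected to run from April 2023 to April 2024.

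**The concern.** There are two separate problems.

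The first is the error rate. A look that weighs effectiveness and can end the trial is a second chance to claim success, unless stopping for benefit is ruled out. The sample size and the final threshold are both set as if there were one chance. The article neither rules out stopping for benefit nor adjusts the final level, so the stated 2.5% one-sided error is not secured.

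The second is the trigger. Half the patients enrolled is not half the information, because each patient's outcome arrives weeks after enrolment. A decision to stop or to change the protocol would rest on much less data than the figure of 159 suggests. The trial is open-label and the interim results are shared with every investigator, so the look can also affect how the remaining patients are managed and assessed.

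**Working it through.** **1. Is the sample size a one-look design?** Inputs from Sample size: control 0.394, probiotic 0.152, margin 0.10, one-sided alpha 0.025, power 80%.

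n per arm = (1.960 + 0.842)² × [0.394 × 0.606 + 0.152 × 0.848] / (0.242 − 0.10)² = 7.849 × 0.3677 / 0.02016 = 143.1.

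Dividing 143 by 0.9 for 10% loss gives 158.9, so 159 per arm and 318 in total. (Rounding 143.1 up to 144 first gives 160 per arm.) The stated 318 is therefore reproduced with the whole 0.025 spent on one analysis and no visible allowance for an interim look.

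**2. Overall error with two looks.** Under the null hypothesis the interim and final Z statistics are bivariate normal with correlation √t, where t is the information fraction. Overall two-sided error = 1 − P(|Z1| < c1 and |Z2| < c2), with c2 = 1.960 (P < 0.05, taken as two-sided).

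| Interim rule for benefit | t = 0.30 | t = 0.36 | t = 0.50 |
|---|---|---|---|
| P < 0.05 (c1 = 1.960), two-sided | 8.9% | 8.75% | 8.3% |
| Same rule, one-sided (stated level 2.5%) | 4.5% | 4.4% | 4.2% |
| P < 0.001, two-sided | 5.05% | 5.04% | 5.02% |
| No stopping for benefit | 5.0% | 5.0% | 5.0% |

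**3. Information at the trigger.**

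- Lag from end of chemotherapy to complete outcome: 21 + 30 = 51 days to 42 + 30 = 72 days, or 1.68 to 2.37 months at 30.44 days per month.
- Accrual, assumed uniform over 12 months: 318 / 12 = 26.5 per month.
- Enrolled without a complete outcome: 26.5 × 1.68 = 44 to 26.5 × 2.37 = 63.
- Complete: 159 − 44 = 115 to 159 − 63 = 96, which is 36% to 30% of 318.

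Other accrual assumptions with the same lag:

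| Accrual (assumed) | Completed outcomes | Share of 318 |
|---|---|---|
| Uniform, 12 months | 96-115 | 30-36% |
| Linear ramp-up, 12 months | 83-102 | 26-32% |
| Uniform, 18 months | 117-129 | 37-41% |
| Uniform, 24 months | 128-137 | 40-43% |

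**4. What a controlled boundary looks like.** A Lan-DeMets spending function of O'Brien-Fleming type, 5% two-sided overall, gives:

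- t = 0.50: interim P < 0.0031, final P < 0.0490 (critical value 1.969 instead of 1.960)
- t = 0.36: interim P < 0.0004, final P < 0.0499
- t = 0.30: interim P < 0.0001, final P < 0.0500 (to four decimals)

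**The case against.** The strongest reply is that the article never says success may be declared at the interim, or at what P value. The words on effectiveness explain why the committee is independent; they are not a stopping rule. The only stopping ground spelt out, under Harms, is obvious harm. Boundaries and the final critical level commonly sit in an analysis plan or committee charter, neither of which is shown, and the 0.05 is a general sentence covering every variable.

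Much of this stands. A reader might infer that the type I error certainly exceeds 5%, or that it is about 9%. The documents support neither. The upper figures need an efficacy test at 0.05 at both looks, which no section states; a look confined to harm or futility inflates nothing. The absence of a boundary from a condensed article is not itself the point. What remains is what the article does state: an effectiveness look with possible termination, next to an unadjusted final level and a one-look sample size.

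On the trigger, the objection is that a look at about a third of the information depends on 12-month uniform accrual, which is an assumption. Also, referred patients who have already finished chemotherapy may enrol later and have a shorter lag. Both are fair, and slower accrual does raise the share. Neither rescues the trigger. Even if every patient enrolled on the day of surgery, a 30-day lag at 26.5 per month leaves 26 of the 159 incomplete, so 133 or 42% of 318.

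**Conclusion.** The point holds in conditional form. If stopping for benefit is possible, a final test at 0.05 does not keep the overall two-sided error at 5%: it lies between about 5.02% (interim P < 0.001) and 8.9% (0.05 at both looks, 30% information). On the article's own one-sided scale the upper end is 4.2-4.5% against 2.5%. If the look can stop only for harm or futility, the error is unaffected. The article does not say which case applies.

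The trigger is a stated rule and is weak in every accrual scenario examined: 30-36% of the planned outcomes under uniform 12-month accrual, 26-32% under ramp-up, and 37-43% if accrual takes 18-24 months. These figures take enrolment to be at the end of chemotherapy and ignore dropout.

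**What to change.** **As a plan.** Define the interim by 159 patients with completed 30-day postoperative outcomes. Then choose one of two options and state it:

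- The look may stop for harm or futility only, with no stopping for benefit. The final test stays at 0.05.
- Stopping for benefit is allowed under a Lan-DeMets spending function of O'Brien-Fleming type: at half information, interim two-sided P about 0.003 and final about 0.049, recomputed at the information actually available. The final level for the primary outcome replaces 0.05 in Statistical methods.

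**Cost.** The second option moves the final critical value from 1.960 to 1.969, with negligible loss of power. The later trigger has a small downside: at 26.5 per month, 159 + 44 = 203 to 159 + 63 = 222 patients are already enrolled by then, so an early stop spares fewer of them.

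**As things stand.** Trial status says that recruitment is complete and the trial has ended, so the trigger can no longer be changed. The report should state whether the look took place, how many completed outcomes it used, and whether stopping for benefit was permitted and under what rule. If it was permitted, the primary outcome should be tested at the final level that follows from that rule and that information. A strict boundary chosen afterwards is no substitute: an interim efficacy threshold of P < 0.05 would already have spent the whole 5%. If stopping for benefit was not permitted, a sentence saying so is enough and 0.05 stands.

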### Interventions, surgery and perioperative management

Patients in the probiotic group will receive three probiotic capsules (BIFICO, live combined *Bifidobacterium*, *Lactobacillus* and *Enterococcus* capsules, Shanghai Sine Pharmaceutical Co. Ltd., [name], Shanghai, China) containing *Bifidobacterium longum, Lactobacillus acidophilus,* and *Enterococcus faecalis* twice per day. Each capsule will contain > 1 * 10^7^ colony-forming units (CFUs) of live bacteria. Patients in the control group will be managed with a blank control. The intervention duration will begin from the end of the last cycle of NACT to postoperative day (POD) 7 or the discharge day. Adherence to the intervention protocols will be checked by telephone before admission to the surgical departments and making the rounds of the wards after admission. If any adverse event associated with the intervention occurs, the intervention will be stopped after evaluation by the investigators.

All enrolled patients will adhere to a perioperative enhanced recovery after surgery (ERAS) protocol [23]. The ERAS program involves preoperative prehabilitation [24] (including physical and respiratory training, nutritional support and psychosocial treatment), no preoperative mechanical bowel preparation, fasting 6 h before surgery and oral glucose solution ingestion allowed until 2 h before surgery, intraoperative target-oriented liquid management, local anesthesia in the deep incision, general anesthesia combined with epidural anesthesia, early removal of the urinary catheter and abdominal drainage tube, early bedside activity, multimodal postoperative analgesia, and postoperative early food ingestion under the guidance of surgeons (from liquid to semi-liquid then solid food according to the tolerance of patients).

Laparoscopic or DaVinci robotic radical gastrectomy will be performed by surgeons from the 22 hospitals whose capacity evaluation is described above. Surgical procedures will be guided by *Japanese Gastric Cancer Treatment Guidelines 2021 (6 th edition)* [2]. The type of digestive tract reconstruction will depend on the habits, intraoperative status and past experience of the surgeons, and the choice of laparoscopy- or DaVinci-assisted surgery will depend on the patients’ choice.

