Notably, all participants cannot intake any drugs containing probiotics and/or prebiotics during the study. Prophylactic antibiotic use is allowed during the operation and should be stopped within 24 h after surgery. Therapeutic antibiotics are allowed to be prescribed if postoperative infections occur, and the type and duration of antibiotic use are based on clinical experience and bacteriologic evidence.

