### Outcomes

The primary outcome is the incidence of postoperative infectious complications, which are defined as bacterial infections occurring within 30 d after surgery. The definition of infectious complications is based on fever (≥ 38 °C), elevation of C-reactive protein (CRP), specific clinical symptoms of infection and positive bacterial culture. The diagnostic criteria for postoperative infections in this study are as follows. Pneumonia [25]: fever, cough, dyspnea, reduced arterial oxygen, typical pulmonary infiltrate on chest X-ray, positive culture from sputum or bronchoalveolar lavage. Urinary tract infection: obvious symptoms including frequent micturition, urgency to urinate, urodynia, leukocyturia, and a positive urine culture with > 10^5^ CFU/ml. Incision infection: redness or swelling of the incision, subcutaneous gas accumulation and purulent secretion and positive culture of incisional secretion [26]. Intraabdominal infection [27]: abdominal symptoms and positive signs such as abdominal pain, tenderness, rebound tenderness, radiographic evidence including intra-abdominal abscess, positive bacterial cultures from intra-abdominal smears or abdominal drainage fluid. Catheter-related blood stream infection: refer to the guidelines [28]. Systemic inflammatory response syndrome (SIRS): two or more of the following: a, temperature > 38 °C or < 36 °C; b, heart rate > 90/min; c, respiratory rate > 20/min or PaCO2 < 32 mm Hg (4.3 kPa); d, white blood cell count > 12 000/mm^3^ or < 4000/mm^3^ or > 10% immature bands [29]. The diagnosis of sepsis should follow the *Sepsis- 3 Consensus* [30].

Secondary outcomes for all participants include blood test results, such as the leukocyte count (WBC), percent of neutrophils (NEUT%), CRP and procalcitonin on PODs 1, 3, and 5; postoperative body temperature; length of postoperative hospital stay (LOS); total cost of hospitalization; 30-d readmission rate; 30-d mortality rate; duration of therapeutic antibiotic use; time to first flatus, first bowel movement and solid food tolerance; time to initiating adjuvant chemotherapy; EORTC QLQ-C30 score [31] on POD 30; PGSAS- 45 score [32] on PODs 3, 5 and 30; and visual analogue scale for pain evaluation on PODs 1, 3 and 5.

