### Assignment of interventions

A central dynamic, stratified strategy was adopted for the aim of randomization. The sequence of randomization was generated by a certain statistician who was independent of this trial using the method of Pocock-Simon minimization by SAS 9.3 (SAS Institute Inc., Cary, NC, USA) and stratified by age (< 65 years old or ≥ 65), tumor location (upper, middle or lower) and preoperative chemotherapy cycles (2 or ≥ 2 cycle). The stratification information provided by the investigators was submitted to the statistician who was responsible for executing randomization. Consequently, the allocation information will then be sent back to each participating site, and investigators will assign given interventions. The statistician is the only one who will know the allocation sequence to ensure that the sequence is concealed until the interventions are assigned.

Due to the open-label design of this study, no one will be blinded after assignment to interventions. After receiving the allocation information, investigators from every participating center will assign the given interventions to participants.

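### Releasing interim results to all investigators of an open-label trial could add an avoidable bias, of unknown size and direction, to two partly clinician-guided secondary outcomes (minor)

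*Protocol article*

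**What the plan says.** All places are in the protocol article.

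- **Data monitoring and auditing.** On the committee: "The DMC remains independent of the research team of the project in order to objectively evaluate the effectiveness and safety". An interim analysis is planned when 159 patients, half of 318, are enrolled. Three decisions are possible, and two of them keep the trial running. The next sentence reads: "The results of the interim analysis will be released to all investigators". No condition is attached.
- **Assignment of interventions.** "no one will be blinded after assignment to interventions", and "investigators from every participating center will assign the given interventions to participants".
- **Interventions, surgery and perioperative management.** If an adverse event is associated with the intervention, "the intervention will be stopped after evaluation by the investigators". The enhanced-recovery programme includes "postoperative early food ingestion under the guidance of surgeons (from liquid to semi-liquid then solid food according to the tolerance of patients". For therapeutic antibiotics after an infection, "the type and duration of antibiotic use are based on clinical experience and bacteriologic evidence".
- **Outcomes.** The secondary outcomes include "duration of therapeutic antibiotic use; time to first flatus, first bowel movement and solid food tolerance".
- **Strengths and limitations.** The article concedes that the surgeon's awareness in an open-label trial may distort results. It does not mention the interim release there.
- **Trial status.** Recruitment is complete, and the trial ended during peer review.

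**The concern.** In an open-label trial, clinicians know which arm each patient is in. They need not know which arm is ahead in that trial. Releasing by-arm interim results while patients are still being treated supplies this second piece of knowledge. Two secondary outcomes are open to it because they depend partly on what clinicians decide: when a patient moves on to solid food, and when therapeutic antibiotics stop. If those decisions shifted with the interim result, a difference in these outcomes would partly reflect the first half of the trial feeding back into the care of the second. It would then be weaker as independent support for the primary result.

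The source is avoidable. An independent committee already exists, and sites need only its decision in order to act.

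**Working it through.** No figure in the article is in dispute. The check is whether the text supports each link in the chain, and how many patients could be exposed.

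**1. What is released.** The monitoring section lists the possible decisions in one sentence and speaks of results in the next. The committee's task covers effectiveness, which in a two-arm trial means a comparison of arms. By-arm results are therefore the natural reading, though not a certain one. No other section limits the release to the decision, to pooled data or to a stopped trial.

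**2. Who receives it.** All investigators. They assign the interventions at every centre and judge whether to stop them after an adverse event. That they are also the surgeons and prescribers is the natural inference, but the article does not state it.

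**3. What they can influence.** Surgeons guide feeding, together with patient tolerance. Antibiotic duration rests on clinical experience, together with bacteriology. Discretion is limited but present, and each decision feeds a listed secondary outcome.

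**4. How many patients could be exposed.**

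Inputs from the article: 318 patients; anticipated recruitment from April 2023 to April 2024 (about 52.18 weeks); surgery 3 to 6 weeks after chemotherapy; a 30-day window for the primary outcome (4.29 weeks); interim at 159 enrolled.

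Assumptions, not in the article: even accrual, randomisation at the end of chemotherapy, and a delay from trigger to release of 0, 4 or 8 weeks.

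Accrual: 318 / 52.18 = 6.09 patients per week.

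*(a) Trigger as written, at the 159th enrolment.* With s the weeks from enrolment to surgery and L the delay, the number operated on before release is 159 + (L − s) × 6.09.

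- L = 0: s = 3 gives 141 before and 177 after; s = 6 gives 122 before and 196 after. That is 56% to 62% after release.
- L = 4 to 8: 128.5 (L = 8, s = 3) to 171.2 (L = 4, s = 6) after release, or 40% to 54%.

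At this trigger only 159 − (s + 4.29) × 6.09 = 115 (s = 3) to 96 (s = 6) patients would have 30-day outcomes. A later analysis is therefore plausible.

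*(b) Trigger when the first 159 reach day 30.* The number operated on before release is 159 + (4.29 + L) × 6.09.

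| L (weeks) | Before | After | Share after |
|---|---|---|---|
| 0 | 185 | 133 | 42% |
| 4 | 209.5 | 108.5 | 34% |
| 8 | 233.9 | 84.1 | 26% |

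Across both triggers, 84 to 196 of 318 patients (26% to 62%) would be operated on after release. A shift in care of size b confined to those patients would enter the overall arm difference at about 0.26b to 0.62b. The article gives nothing from which b, or its sign, could be derived.

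**The case against.** **The sentence may mean only the decision.** It follows directly on the three possible decisions, and the Harms section also has the committee informing all investigators, there before a stop for harm. On that reading no bias is added. This stands as a real possibility, and the conclusion is conditional on it. A reader might infer that by-arm results were actually circulated; the article does not say so. Nor is this merely detail that a journal article leaves to a fuller document, because the sentence states a release without limit.

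**The increment over existing bias is not shown.** Clinicians already know the arm, and the sample size section cites infection rates of 39.4% and 15.2% from the group's previous single-centre trial, so expectation already favours probiotics. An interim result weaker than that could temper the expectation. This stands: a reader might infer a bias in favour of probiotics, but the direction is unknown. What remains is that comparative data from the trial itself are a separate source of influence, which the conceded limitation does not cover.

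**Discretion is limited.** The abstract says that other perioperative management is the same in both groups. All patients follow one enhanced-recovery protocol, feeding depends on tolerance, and antibiotics depend also on bacteriology. This narrows the room for bias but does not close it. The line on stopping the intervention after an adverse event has no bearing on diet or antibiotic duration; it only helps to show the investigators' clinical role.

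**Changing the rule protects no patient now.** Correct. For this trial the remedy is disclosure and cautious interpretation.

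**Conclusion.** The point holds as a minor one. As written, the rule permits release of comparative interim results to the clinicians of a continuing open-label trial. On the natural reading it could add an avoidable bias to time to solid food tolerance and duration of therapeutic antibiotics, beyond the open-label bias already conceded.

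This rests on two inferences: that the results are by arm, and that the investigators are the treating clinicians. The exposed share of 26% to 62% rests on assumed accrual and timing and measures exposure, not bias.

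Two stronger readings are not supported. A reader might infer a specific rise in the false-positive rate for these outcomes. Any such figure would need an assumed shift in care, an assumed standard deviation and an assumed release date, none of which the article gives. A reader might also infer that the primary result is compromised. Its definition relies on cultures and other listed clinical, laboratory and imaging criteria, and nothing in the article shows how a release would change it.

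**What to change.** **Rule.** Replace the release sentence so that interim comparisons between arms stay within the independent monitoring committee, and sites receive only one of its three decisions: continue, continue with an adjusted protocol, or terminate.

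**This trial.** State in the report whether interim results were released, when, and in what form.

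- If only the decision was released, one clarifying line is enough.
- If by-arm results went out, keep both outcomes as planned secondary outcomes, describe them as open to performance bias, and do not present them as independent corroboration of the primary result.

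**Cost.** A sentence or two and a look at the sponsor's records; the article does not show whether a release took place. No planned analysis changes and no additional analysis is needed. Disclosure does not remove the ordinary open-label bias.
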